**Primary**					
	The percentage of patients having hospital re-presentation (emergency department presentation with or without hospital admission) within 3 months of discharge from the index admission			Re-presentation data available from the electronic medical record Statistical analysis: comparison of proportions between treatment and control groups and time to re-presentation analysis using the log-rank test with the method of Kaplan-Meier [55]	

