### Data Collection

The pRCT will use a mixed methods approach to data collection, primarily quantitative with a qualitative descriptive component. Data will be gathered through validated patient assessment and transition instruments (Table 1), electronic medical record reviews, phone call support and monitoring, and interviews.

**Table 1 table1:** Data collection instruments, characteristics, and analysis methods.

Instrument	Number of items and response options	Analysis method
Community Assessment Risk Screen [41,42]	Three items (ranging 0-9): 0-3 (low risk); 4-9 (high risk)	Quantitative
Customized transition nursing assessment [43]	A total of 28 summary items	Quantitative and qualitative: open-ended narrative comments from participants
EQ-5D-3L health questionnaire [44]	Five dimensions: mobility, self-care, usual activities, pain or discomfort, and anxiety or depression and patient’s self-rated health on a vertical visual analog scale	Quantitative and qualitative: open-ended narrative comments from participants
Patient Continuity of Care Questionnaire (short) [45]	A total of 12 items	Quantitative and qualitative: open-ended narrative comments from participants
Barthel Index [46]	A scale describing 10 tasks scored according to the amount of time or assistance required by the patient; total score from 0 to 100, with lower scores representing greater nursing dependency	Quantitative
Edmonton Frailty Scale [47,48]	A scale sampling 10 domains, where the maximum score is 17, representing the highest level of frailty	Quantitative
Kessler Psychological Distress Scale [49]	A 10-Item measure designed to assess nonspecific psychological distress	Quantitative
Malnutrition Universal Screening Tool [50]	Three independent criteria are assessed: BMI score, weight loss score, and acute disease effect score; all scores are added, where 0 indicates low risk, 1 indicates medium risk, and a score of 2≥ indicates high risk	Quantitative
General Self-Efficacy Scale [51]	A 10-item scale for a self-rated measurement of self-efficacy; total score between 10 and 40, with higher scores indicating higher self-efficacy	Quantitative and qualitative: open-ended narrative comments from participants
Edmonton Symptom Assessment System [52]	Measures symptom burden of chronic disease and has evolved into an 11-point numeric rating scale, ranging from 0 (no symptom) to 10 (worst possible)	Quantitative

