### Statistical Analysis

An intention-to-treat approach will be used. Linear regression analyses will be conducted to estimate the effects of the intervention on primary and secondary outcomes. A fixed effects model will be used to account for stratification at the hospital and unit levels. Sensitivity analyses will be performed to assess the robustness of the findings. Table 2 presents the alignment of data analysis with primary and secondary study outcomes.

**Table 2 table2:** Primary and secondary outcomes—measurement and statistical analysis.

Outcome					Data source, measurement, and analysis

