### Identification and Recruitment of Participants

Several procedures to identify and recruit participants for the trial intervention have been incorporated into the study design.

Nursing, medical, pharmacy, and allied health leads and managers; ward staff; and patient flow and bed management meetings will be attended by the research leads and STARnurses to brief staff and explain all aspects of the research and introduce the STARnurses and their role. Emails and flyers will be sent by the research leads to medical, nursing, pharmacy, and allied health leads as well as relevant clinical staff.

Study criteria will be entered into the local electronic medical record to produce a trial list of potential participants. The STARnurses will review the list daily and follow up with relevant treating clinicians. Daily rounds will be conducted at trial wards, and nursing staff will liaise with medical staff to identify patients. Huddles will be attended, and nursing staff will liaise with medical staff to identify patients.

The patient’s clinical team will be consulted first, and if permission is granted, a research team member will then approach the patient. They will be invited to participate in the study, and if they accept, they will be provided with a participant information sheet and consent form for consideration. The patient will then be approached 24 hours later to confirm their willingness to participate. Individual randomization using REDCap will take place following informed written consent [53].

It is acknowledged that participants who provide consent will have multimorbidity and may even be frail, and the collaboration with their multidisciplinary team will be an integral component of the intervention. Therefore, balancing the participant’s agency and self-efficacy and capability with their anxiety and hesitancy will require ongoing discussion between the participant and team members, along with their support.

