### Intervention

The intervention involves establishing a transition coordination service led by nursing transition coordinators, who will support transitions and referrals, known as STARnurses. The intervention consists of 4 key phases.

The first phase involves in-hospital screening in which “risk of readmission” screening is conducted during the hospital stay, using the Community Assessment Risk Screen tool [41,42]. Patients who meet the inclusion criteria are invited to participate in the study.

The second phase involves in-hospital baseline assessment, transition planning, and participant goal setting (following participant research and information discussion, acceptance to participate, and consent procedure complete). A detailed inpatient baseline and transition assessment is performed to collaboratively develop personalized goals and a transition action plan. Researchers will use the following tools to assess participants’ transition needs: customized transition nursing assessment [43], Barthel Index [46], Edmonton Frailty Scale [47,48], Kessler Psychological Distress Scale [49], Malnutrition Universal Screening Tool scale [50], and General Self-Efficacy Scale [51]. The participant’s GP or practice nurse will be contacted and receive the transition action plan before the participant’s hospital discharge.

The third phase is posthospital discharge transition coordination. Participants will receive transitional care coordination, with phone calls or telehealth follow-up in the first 48 hours following discharge and then weekly and fortnightly (Figure 1).

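### The stated primary analyses leave out the pre-randomisation readmission-risk score (0-9); adding it as one baseline covariate would give a modest gain in precision at no data cost

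*Protocol article*

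**What the plan says.** Two places in the protocol article fix the analysis of the primary outcome.

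- Table 2 (Primary): "Statistical analysis: comparison of proportions between treatment and control groups", followed by a Kaplan-Meier and log-rank analysis of time to re-presentation. No covariate is named.
- Statistical Analysis: "Linear regression analyses will be conducted to estimate the effects of the intervention on primary and secondary outcomes", and then "A fixed effects model will be used to account for stratification at the hospital and unit levels". Hospital and unit are the only adjustment terms given.

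Three places describe the score and its timing.

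- Table 1 (Data Collection) gives its form: "Three items (ranging 0-9): 0-3 (low risk); 4-9 (high risk").
- Intervention, first phase: "screening is conducted during the hospital stay, using the Community Assessment Risk Screen tool". Invitation to take part comes after this step in the text.
- Identification and Recruitment of Participants: "Individual randomization using REDCap will take place following informed written consent".

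The Randomization section stratifies by ward or unit only. The Eligibility Criteria set no threshold on the score.

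**The concern.** The trial has a numerical baseline measure whose purpose is to predict the kind of event that forms the primary outcome. It is taken before allocation, so treatment cannot influence it. The design does not balance it across arms, and neither stated analysis uses it.

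Adjusting for a prognostic baseline variable removes the part of the between-arm difference that comes from chance imbalance in that variable, and so narrows the confidence interval. Without it, the trial accepts a wider interval than its own data require. Enrolment closed on March 31, 2025, so the sample can no longer grow, and the analysis is one of the few places where precision can still be gained.

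**Working it through.** **Inputs**
- Sample: about 200 patients at 1:1, so 100 per arm (Sample Size Estimation and Justification; Randomization).
- Control rate 35, 40 or 45%; absolute reduction 15, 20 or 25 points; 80% power; α = 0.05 (Table 3). Sidedness is not stated; two-sided reproduces the table.
- R², the share of outcome variance explained by the score: not in the documents. Assumed 0.05 to 0.15.

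**Step 1. Reproduce Table 3.** n per group = (1.960 + 0.842)² × [p1(1−p1) + p2(1−p2)] / (p1−p2)², rounded up.
- 40% vs 25%: 7.849 × (0.2400 + 0.1875) / 0.0225 = 149.1, so 150. Table 3 has 150.
- 40% vs 20%: 7.849 × (0.24 + 0.16) / 0.04 = 78.5, so 79. Table 3 has 79.

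All nine cells reproduce exactly.

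**Step 2. Power without the score, 100 per arm.** Power = Φ[(d − 1.96·SE0)/SE1], where SE0 uses the pooled proportion and SE1 the separate ones.
- 40% vs 25%: SE0 = √(2 × 0.325 × 0.675/100) = 0.0662; SE1 = √(0.4275/100) = 0.0654; Φ(0.309) = 62.1%.
- 40% vs 20%: SE0 = √(2 × 0.30 × 0.70/100) = 0.0648; SE1 = √(0.40/100) = 0.0632; Φ(1.154) = 87.6%.

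For control rates 35/40/45%, power is 66/62/59% at 15 points, 91/88/85% at 20 points and 99/98/97% at 25 points.

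**Step 3. Power with the score.** Adjustment multiplies the variance by about (1 − R²), which acts like a sample of 100/(1 − R²) per arm. Control rate 40%:

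| Assumed R² | Effective n per arm | Power, 15 points | Power, 20 points | Difference detectable at 80% power |
|---|---|---|---|---|
| 0 | 100 | 62.1% | 87.6% | 18.2 points |
| 0.05 | 105.3 | 64.4% | 89.2% | 17.8 points |
| 0.10 | 111.1 | 66.7% | 90.7% | 17.3 points |
| 0.15 | 117.6 | 69.2% | 92.2% | 16.9 points |

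The gain equals about 5 to 18 extra patients per arm.

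**Step 4. Check by simulation.** 8,000 trials per setting, a 0-9 score, 40% control rate, and a linear model with robust standard errors against the unadjusted test. AUC is the score's discrimination for the outcome, also an assumption.

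| AUC | R² | 15 points, unadjusted → adjusted | 20 points, unadjusted → adjusted |
|---|---|---|---|
| 0.50 | 0 | 62.8% → 62.8% | 87.3% → 87.4% |
| 0.60 | 0.03 | 62.9% → 63.9% | 87.5% → 88.7% |
| 0.65 | 0.07 | 62.2% → 64.7% | 87.4% → 89.3% |
| 0.70 | 0.12 | 62.8% → 67.2% | 88.1% → 91.2% |
| 0.75 | 0.19 | 62.3% → 69.8% | 87.3% → 92.0% |

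The simulation agrees with the formula. A score with no predictive value costs nothing visible, and the top of the assumed R² range needs an AUC above 0.70.

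**The case against.** **Covariates belong in the SAP, which is not shown.** This is the strongest objection. A condensed article that merely omitted covariates would be no finding. Here, however, the article names the test in Table 2 and the adjustment terms in the text, and the score is in neither. If the SAP already includes it, only the article's description needs aligning.

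**The plan is not purely unadjusted.** This is correct. Someone reading Table 2 alone might infer that the primary analysis is a raw comparison and nothing more, but the Statistical Analysis section plans a regression with hospital and unit effects for the same outcome. The score is missing from both. The article does not say which analysis is primary, so naming one model would settle that too.

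**The trial is not short of power throughout.** This is also correct. A reader might infer from the 15-point row that there is little power to spare. Table 3 does not support that in general: 100 per arm exceeds every 20-point cell (70/79/86) and every 25-point cell (40/47/52). The 20-point margin narrows with losses, to 86/82/79% if 15% are lost (85 per arm; the loss rate is assumed). At 15 points and a 40% control rate, even R² = 0.15 reaches only 69%, so adjustment does not rescue that scenario.

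**The unadjusted comparison is valid.** A reader might infer bias from possible imbalance in the score. Individual randomisation rules that out, and the unadjusted standard error already allows for chance imbalance. Only efficiency is at issue.

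**The size of the gain is assumed, and complete collection is inferred.** Both stand. No passage links score to outcome. The screening step is described under Intervention, and the documents do not say how its result is used. If it guides selection in practice, the range of scores narrows and the gain shrinks.

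**It is late to prespecify.** Enrolment and data collection are reported as complete, so the choice is credible only if made before outcomes are compared by arm.

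**Conclusion.** The point holds as an improvement in efficiency. The stated primary analyses leave unused a readmission-risk score measured before randomisation. Nothing in Table 3 is wrong and the planned comparison is unbiased.

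At 100 per arm and a 40% control rate, the gain is about 2 to 7 percentage points of power for a 15-point reduction and about 2 to 5 for a 20-point reduction. This assumes R² of 0.05 to 0.15, no losses, and a score available for every participant. With weaker prediction the gain falls towards zero, with no material penalty. It is worth doing because it is almost free. The trial's adequacy does not depend on it.

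**What to change.** Before outcomes are compared by arm, record the following in a dated SAP or amendment.

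1. The primary analysis is the unit-adjusted regression already planned in the Statistical Analysis section, with the Community Assessment Risk Screen score (continuous, 0-9) as one added baseline covariate.
2. The reported effect is the marginal difference in 3-month re-presentation risk, with robust standard errors.
3. The raw proportions by arm are shown alongside.
4. Each participant's score is confirmed as present and dated before randomisation, with a stated rule for any that are missing.

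If outcomes have already been compared by arm, the adjusted model should be presented as a sensitivity analysis and labelled as chosen afterwards.

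The cost is a short addition to the analysis text and a completeness check on a variable that the protocol already collects. No new data are needed.

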**Secondary**					
	**Health care use**				
		The rate of hospital re-presentation within 1, 6, and 12 months of discharge from the index admission	Readmission data available from electronic medical record Rate defined as the number of re-presentations over a unit of time (eg, 1 y) Statistical analysis: nonparametric comparison of rates of re-presentation between treatment and control groups		
		Overall length of hospital stay within 1, 3, 6, and 12 months of discharge from the index admission	Readmission data available from electronic medical record Defined as the cumulative number of days spent in hospital over a unit of time (eg, d/y) Statistical analysis: nonparametric comparison of rates of re-presentation between treatment and control groups		
		Cost of transition service	Economic benefits of the intervention will be confirmed through a comparison of subsequent rehospitalization costs in the treatment and control groups		

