	**Organization of care**				
		Implementation of components of the TCM^d^	Economic benefits: cost calculations of comparison between control and intervention hospital readmissions from the index admission Includes TCM intervention cost compared with usual care cost		
		Implementation of the transition action plan for all patients	Customized transition action plan developed		

^a^ESAS: Edmonton Symptom Assessment System.

^b^GSE: General Self-Efficacy Scale.

^c^PCCQ: Patient Continuity of Care Questionnaire.

^d^TCM: transitional care model.

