## Discussion

### Anticipated Findings

The primary outcome of this research is decreasing the rate of hospital readmission within 3 months of discharge from the index admission in people with multimorbidity. In a prospective, quasi-experimental TCM study (N=172), improvements in all health status and quality of life measures were observed after intervention compared to before the intervention, and a significant decrease in total number of readmissions (TCM: 45 readmissions vs control: 60 readmissions; *P*<.041) and total hospital days (TCM: 252 d vs control: 351 d; *P*<.032) were observed at 3 months [57].

The secondary outcomes include the cost analysis of the transition service model of care. In a previous study, cost savings were demonstrated in relation to appropriate implementation of the TCM, whereby it was associated with a short-term decrease of US $439 per patient per month in total health care costs at 3 months and cumulative per-patient savings of US $2170 at 1 year (*P*<.037). In a cost comparison study in which the post–acute care costs of 3 care management interventions for hospitalized older adults with cognitive impairment and their family caregivers were compared (N202), the TCM had significantly lower costs than 2 other comparable care management interventions and has been associated with an estimated net savings of US $2972 per individual at 6 months [26].

People with multimorbidity are readmitted to the hospital more, spend more time seeking health care, and often receive fragmented care. When they are discharged from the hospital, they are often readmitted due to poor health care team communication, uncoordinated follow-ups, and not knowing whom to contact when they have symptoms. Supporting these patients as they transition to the community after hospital discharge with an adapted nurse-led TCM intervention will assist them to resume their normal lives more quickly and prevent unnecessary hospital contact.

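### Bed-days and hospital costs are counted from index discharge, although randomisation and the in-hospital part of the intervention come earlier, so any effect on the remaining index stay is not captured

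*Protocol article*

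**What the plan says.** **Outcome window.** Table 2 (Health care use) lists "Overall length of hospital stay within 1, 3, 6, and 12 months of discharge from the index admission". The source is given as "Readmission data available from electronic medical record", and the measure is "Defined as the cumulative number of days spent in hospital over a unit of time".

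**Costs.** The same part of Table 2 says "Economic benefits of the intervention will be confirmed through a comparison of subsequent rehospitalization costs in the treatment and control groups". Under Organization of care, the cost item is described as "cost calculations of comparison between control and intervention hospital readmissions from the index admission", and the next line adds the cost of the intervention against the cost of usual care.

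**Timing of allocation and treatment.** The inclusion criteria require inpatients, on a ward or in the emergency department. The recruitment section states "Individual randomization using REDCap will take place following informed written consent". The Intervention section places phase 2 (baseline assessment, goal setting and the transition action plan) in hospital. It also says that the GP or practice nurse is to be "contacted and receive the transition action plan before the" patient leaves hospital.

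**The concern.** Index discharge is an event after randomisation, and its timing could depend on the allocated arm. The intervention places planning work and a handover to primary care before discharge. That work might hold a discharge back, or better planning might bring it forward. The bed-day outcome and the hospital cost comparison start the clock at discharge, so a change of either kind would not be seen.

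At stake is what the trial may conclude about hospital use and money. If the index stay became longer in the intervention arm, the trial could report fewer bed-days and lower hospital costs while total use after randomisation had not fallen by that amount. If the stay became shorter, a real saving would be missed. The article calls the outcome overall length of stay, and its Conclusions look forward to a fall in overall health care use. The measure as defined cannot by itself support a statement that wide.

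**Working it through.** The plan gives no figure of its own for bed-days or cost. Its only sample-size figures, in Table 3, concern the 3-month primary outcome, and nothing here changes them. The check is therefore mainly one of timing.

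**1. Order of events in the article**

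| Step | Where stated | Before or after index discharge |
|---|---|---|
| Consent, then randomisation | Identification and Recruitment of Participants | before |
| Phase 2: assessment, goals, action plan; plan sent to GP or practice nurse | Intervention | before |
| Counting of bed-days starts | Table 2, Health care use | at discharge |
| Counting of hospital costs starts | Table 2, Health care use and Organization of care | readmissions only |
| Intervention cost against usual care cost | Table 2, Organization of care | not limited to either side |

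No section makes index days after randomisation an outcome or a cost item. The usual-care cost line does not fill the gap, because the Control section defines usual care as planned follow-up services.

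**2. What is and is not estimated**

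Let I be the days from randomisation to index discharge and P the hospital days after discharge. Leaving aside where the window closes, hospital days after randomisation are T = I + P, and the difference between arms is

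ΔT = ΔI + ΔP.

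Table 2 estimates ΔP. It equals ΔT only if ΔI = 0, which the article neither shows nor plans to check.

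**3. Scale, as illustration only**

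The one bed-day effect cited (Anticipated Findings) is "total hospital days (TCM: 252 d vs control: 351 d") at 3 months, from a quasi-experimental study of 172 patients. Arm sizes are not given, so days per patient depend on an assumed split:

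| Assumed split (TCM/control) | TCM | Control | TCM minus control |
|---|---|---|---|
| 70/102 | 252/70 = 3.60 | 351/102 = 3.44 | +0.16 |
| 86/86 | 252/86 = 2.93 | 351/86 = 4.08 | −1.15 |
| 100/72 | 252/100 = 2.52 | 351/72 = 4.875 | −2.36 |

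Even the sign depends on the split. Taking the equal split and some hypothetical values of ΔI:

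| ΔI (days) | ΔP, as Table 2 would report | ΔT |
|---|---|---|
| −1 | −1.15 | −2.15 |
| 0 | −1.15 | −1.15 |
| +0.5 | −1.15 | −0.65 |
| +1 | −1.15 | −0.15 |
| +1.15 | −1.15 | 0 |

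The reported figure is the same in every row. The values of ΔI are not taken from the article; they only show that a shift of about a day would matter if the true effect were of this order.

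**The case against.** **The outcome matches the stated objective.** The abstract and the aims measure hospital use from index discharge, and the hypothesis concerns support given after discharge. Counting from discharge is a legitimate readmission measure. This stands, and the outcome should be kept. It does not license a conclusion about total hospital use or net saving after randomisation.

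**No effect on the index stay is shown.** The article does not make discharge wait for the plan to reach the GP, and it gives the transition nurses no control over discharge. The 24-hour interval for considering consent precedes randomisation and so cannot differ by arm. This also stands. A reader might infer that the bed-day and cost results are biased, or that a saving would be spurious. The article supports only that they can be biased, in an unknown direction and by an unknown amount.

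**Costs do not all start at discharge.** A reader might infer that in-hospital nurse work is left out too. Table 2 includes the intervention cost with no limit to the post-discharge period, so that work can be counted. What is missing is the cost of index bed-days after randomisation. A full list of cost items may well sit in a document not shown, but the article itself fixes the hospital component as readmissions.

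**The cited effect is weak evidence of size.** Agreed: with arm sizes unknown, no percentage of it cancelled should be quoted as a finding.

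**Conclusion.** The point holds in a limited form. Allocation and part of the intervention precede the moment at which bed-days and hospital costs begin to count, so an effect on the remaining index stay would be missed, and a bed-day or cost-saving conclusion can be biased either way. This follows from the article's own timing and needs no numerical assumption. The size is unknown: the 1.15-day figure rests on an assumed equal split, and other splits run from 0.16 days more to 2.36 fewer.

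Only secondary outcomes are concerned. A reader might extend the point to the primary outcome because it too runs from discharge. It measures whether a patient comes back within 3 months, so it has no index bed-days to omit, and the sample size is unchanged. This is an inexpensive improvement to the analysis, not a fault in the trial's main comparison.

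**What to change.** 1. Keep the from-discharge bed-day and cost outcomes as stated.
2. Report days from randomisation to index discharge by arm. This shows directly whether the concern has any substance.
3. Add cumulative hospital days and hospital costs from randomisation (remaining index stay plus all later stays) over fixed horizons measured from randomisation, for example 3, 6 and 12 months. A window that opens at randomisation but closes a set time after discharge would not do, because its length would still depend on discharge timing and could differ between arms.
4. Base any claim about overall hospital use or net cost saving on the count in step 3, with the intervention cost included as already planned.

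**Cost.** No new patients or contacts are needed. Randomisation is done in REDCap, and the discharge date is already needed for Table 2. A horizon from randomisation also closes earlier than one of the same length from discharge, so follow-up is not extended. The work is a little more analysis, with a cost attached to the remaining index days. The real downside is variance: index stays of up to 3 weeks are eligible, so the added noise may not be small, and the count from randomisation may be less precise than the from-discharge one. That is a reason to show both.

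### Table 2 assigns length of stay a comparison of re-presentation rates instead of hospital days, and its two utilisation rows do not match the regression planned in the Statistical Analysis text

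*Protocol article*

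**What the plan says.** In Table 2 of the protocol article, under Health care use, the second row is "Overall length of hospital stay within 1, 3, 6, and 12 months of discharge from the index admission". Its definition and its analysis stand next to each other in one entry: "cumulative number of days spent in hospital over a unit of time (eg, d/y) Statistical analysis: nonparametric comparison of rates of re-presentation". The analysis sentence in full reads "Statistical analysis: nonparametric comparison of rates of re-presentation between treatment and control groups".

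The row above, for re-presentation within 1, 6 and 12 months, has the definition "Rate defined as the number of re-presentations over a unit of time (eg, 1 y") and exactly the same analysis sentence.

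The Statistical Analysis section, which introduces Table 2 as the alignment of analyses with outcomes, says "Linear regression analyses will be conducted to estimate the effects of the intervention on primary and secondary outcomes". It continues: "A fixed effects model will be used to account for stratification at the hospital and unit levels". The Randomization section states that allocation is stratified by ward or unit.

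The only time-to-event method in the table belongs to the primary outcome: "time to re-presentation analysis using the log-rank test with the method of Kaplan-Meier".

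**The concern.** There are two faults, both in what the article states and not in what it leaves out.

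First, the outcome and its analysis in the length-of-stay row are different variables. Re-presentation, as the primary row defines it, includes emergency department presentations without admission. Such a visit adds one to the count and little or nothing to hospital days, while one long readmission adds one to the count and many days. A test on one cannot stand in for a test on the other.

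Second, the text and the table give different methods for the same secondary outcomes. The text promises model-based effect estimates that respect the strata. The table gives a two-group nonparametric comparison that mentions neither strata nor an effect measure.

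At stake is whether the published plan fixes the analysis of two utilisation outcomes. Where a plan can be read in two ways, the choice may be made after the data are seen. The stated objective of quantifying the re-presentation rate also needs an estimate with its precision.

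**Working it through.** **1. The two rows side by side**

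| | Re-presentation row | Length-of-stay row |
|---|---|---|
| Windows (months) | 1, 6, 12 | 1, 3, 6, 12 |
| Variable defined | number of re-presentations per unit time | hospital days per unit time |
| Variable in the analysis | re-presentation rate | re-presentation rate |
| Method | nonparametric, two groups | nonparametric, two groups |
| Strata or effect measure | none stated | none stated |

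Read literally, the length-of-stay row repeats the comparison above it at 1, 6 and 12 months and adds a re-presentation comparison at 3 months. Table 2 specifies a comparison of bed-days at 0 of 4 windows.

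**2. The article treats the two quantities as distinct elsewhere.** Anticipated Findings cites a quasi-experimental study that reports readmissions (45 vs 60, ratio 45/60 = 0.75) and hospital days (252 vs 351, ratio 252/351 = 0.72) as separate results, each with its own P value.

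**3. Text against table.** If the Statistical Analysis text governs, each utilisation outcome gets a mean difference from linear regression with stratum fixed effects, and the table's nonparametric wording has no stated role. If Table 2 governs, the fixed effects and the effect estimate are absent from these rows. The article does not say which is the analysis of record, or that one is for estimation and the other for testing.

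**4. Sample size.** Table 3 is the only stated calculation and concerns the primary outcome. With two-sided alpha 0.05 and 80% power, n per group = (1.960 + 0.842)² × [p1(1−p1) + p2(1−p2)] / d². For 35% vs 15%: 7.849 × (0.2275 + 0.1275) / 0.20² = 69.7, so 70, as printed. All nine cells reproduce this way. None depends on the utilisation rows.

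**5. Does the method wording imply a power loss?** The documents give no event rate, dispersion or rate ratio, so these are assumptions. Simulated power with 100 per arm and negative binomial counts:

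| Control mean, dispersion, rate ratio | Mann-Whitney | Negative binomial | Comparison of means |
|---|---|---|---|
| 2, 1, 0.65 | 55% | 68% | 66% |
| 2, 1.5, 0.65 | 42% | 56% | 55% |
| 0.7, 1, 0.6 | 50% | 57% | 55% |

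An unadjusted comparison of means, standing in for the planned linear regression, recovers nearly all of the difference. If instead the intervention lowers the share with any re-presentation (55% vs 38%) and leaves counts among re-presenters unchanged, the order reverses: about 62% for Mann-Whitney and 39% for negative binomial.

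**6. Does it imply bias from deaths?** Mortality is not given, so a range is assumed. True rate ratio 1.0 over 12 months, mean 1.5 per year, dispersion 1.5, 100 per arm, Mann-Whitney on raw counts:

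| Deaths, control vs intervention | Rejection | Crude ratio of mean counts | Ratio per time alive |
|---|---|---|---|
| 15% vs 15% | 5.1% | 1.00 | 1.00 |
| 10% vs 20% | 6.0% | 0.945 | 1.00 |
| 10% vs 30% | 9.5% | 0.89 | 1.00 |

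Distortion needs unequal mortality (or unequal observation) and a denominator that ignores it.

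**The case against.** The strongest reply is that the length-of-stay sentence is an obvious carry-over from the row above, and that the Statistical Analysis section already plans linear regression with fixed effects for secondary outcomes, which include length of stay. On that reading a stratum-adjusted mean difference in bed-days with a confidence interval is planned, and the nonparametric comparison is a supplementary test. This stands in part. A reader might infer from Table 2 that bed-days are never analysed, or that only a P value will be reported. Neither holds for the document as a whole. It remains that the table names the wrong variable, and that nothing says how the two methods relate.

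A second reply is that no rank test is named, since a nonparametric comparison could be a stratified, permutation or bootstrap procedure. This stands. The fair criticism is that the rows mention no strata, not that the method could not carry them.

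A third concerns time at risk. A reader might infer that a patient followed for 2 months is treated like one followed for 12. The article does not say so: both outcomes are per unit of time with the denominator undefined, and handling of deaths and censoring is commonly left to the full plan. One feature makes a clear denominator worth having. Enrolment and data collection are both said to end on March 31, 2025. If records stopped then, and accrual was uniform over about 14 months, complete follow-up would be possible for (14 − 6)/14 = 57% of patients at 6 months and (14 − 12)/14 = 14% at 12 months. Results are due in March 2026, however, so later extraction from records is quite possible.

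**Conclusion.** The point holds as two internal inconsistencies. The length-of-stay row names the wrong variable, so Table 2 specifies no bed-day comparison at any of its four windows; this rests on reading alone and needs no assumption. The two utilisation rows also disagree with the Statistical Analysis text on stratification and on effect estimation.

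The size is modest: secondary outcomes only, with no numerical effect on the primary analysis or on Table 3. A reader might go further and conclude that the plan loses power or is biased by deaths. The documents do not support either. The power ranking depends on assumed event patterns and reverses under one of them, and the mortality distortion vanishes when deaths are balanced. The correction is worth making because it is specific and nearly free.

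**What to change.** 1. In the length-of-stay row of Table 2, replace the re-presentation wording with a comparison of cumulative hospital days between arms at each listed window.
2. Reconcile Table 2 with the Statistical Analysis section: name one main analysis per utilisation outcome, include the randomisation strata (ward or unit), and report an effect estimate with a 95% confidence interval. If a nonparametric test is kept, state that it is supplementary.
3. Suitable forms, as examples: for bed-days, a ward-adjusted mean difference with a bootstrap confidence interval; for re-presentations, a rate ratio from a count regression with observed follow-up time as the denominator.

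The cost is a few words in the table or the analysis plan, slightly more analysis work, and follow-up dates from the record. No change to recruitment, data collection or the primary analysis is needed. Since data collection is reported as finished, the correction should be dated before the utilisation outcomes are compared by arm.
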